### Study sample size

Taking into account that the EB rate in Andalusia is 25%, this is considered the expected value in the control group. An estimated increase effect of 12% of the EB rates at 6 months is established, as asserted in previous studies [34]. To reach this difference between both groups, a two-tail hypothesis is set out, with a power of 80% and assuming a type I error of 5%, assuming a loss of 10% in the follow-up, the necessary sample increases to 512 women, 256 in each group. Missing values in the follow-up will be addressed by multiple imputation technique, performing attrition analysis.

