## Background

In 2003, the World Health Organization (WHO) recommended exclusive breastfeeding (EB) during the newborn’s first 6 months of life and, if possible, during the first 2 years [1]. Breastfeeding is considered the best option to feed newborns due to its multiple properties. However, EB rates resist these recommendations. In developed countries, only 1 out of 3 babies is breastfed during its first 6 months of life, and great differences between areas and countries can be observed [2]. Only 35% of the newborns receive breastfeeding at 3–4 months of age [3].

The percentage of newborns that initiate breastfeeding in their first hour of life has significant importance, since it has been proven that early initiation of breastfeeding after birth is associated with a longer duration of this practice [4]. Despite all the benefits that have been described in the previous literature, for the mother as well as for the newborn at a physical and psychosocial level [5–8], breastfeeding rates after hospital discharge are roughly 71% [9], with a considerable decrease in the first weeks of the newborn’s life, reaching 25% at 6 months postpartum [10]. However, some studies suggest that these women felt disappointed because they could not prolong breastfeeding any longer. Usually, women who ceased breastfeeding after the first 6 weeks postpartum would have wanted to continue for longer, as well as those who breastfed for at least 6 months [1]. The main reasons described were lack of knowledge and of milk production [2]. Thus, it is brought to light that women have a positive inclination to continue breastfeeding but, due to diverse reasons, they are forced to give it up.

A recently published systematic review (2015) identifies the barriers and facilitators related to breastfeeding sustainment; experiences with previous births, certain birth-related hospital practices, or the fact that the mother had been breastfed by her own mother are some of the factors that condition the current breastfeeding experience [11].

Furthermore, there are also factors such as maternal age, schooling level, family support, multiparity or antenatal lessons, that can condition prolongation [12]. On the other hand, it has been observed how other collectives are more vulnerable to breastfeeding sustainment, such as those who have a low socioeconomic status or immigrants, who require greater support from the health professionals [13].

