### Study design

This is a multicentric cluster randomized controlled trial with a control group and an intervention group, without blinding. This protocol has been written according to the recommendations of the SPIRIT 2013 statement [18, 19], a guideline that defines the standard elements of a protocol, including recommendations for intervention trials, which can be found in Additional file 1. Besides, the design of this clinical trial follows the requirements of the CONSORT statement.

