#### Inclusion criteria

Healthy women with exclusive or partial breastfeeding 10 days after birth, and who attended antenatal lessons in the Primary Health CentreWomen over 18 years of ageWomen who accepted and signed the informed consent

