### Analysis

A complete statistical analysis plan will be previously performed, as well as a report thereof and of the results, according to the Consolidated Standards of Reporting Trials (CONSORT) [35, 36]. The analysis will be carried out on the basis of an intention-to-treat principle, without taking into account whether or not adherence to the breastfeeding support group was completed. Individual health centres are the randomization units and the mother-newborn dyad will be the analysis unit. All statistical trials and confidence intervals will be assumed with a type I error established in alpha = 0.05, using the IBM SPSS V22 statistics package [37].

An exploratory data analysis will be conducted in order to identify atypical values, for the total of our studied sample, as well as for the different sub-groups created. A graphic exploratory analysis of the different studied variables will also be conducted, according to their numerical or non-numerical character. Frequency and percentage distribution scales will be elaborated for the descriptive analysis of variables with a qualitative (non-numerical) character. For the quantitative (numerical) ones, centralization and dispersion measures will be calculated. In variables with a normal distribution, the mean and the standard deviation will be calculated and, in those with an asymmetric distribution, the mean and interquartile range (p25-p75) will be calculated. Furthermore, point estimators and confidence intervals will be calculated at 95% for averages and percentages. The relationship between two qualitative variables will be analysed with Pearson’s chi-square test, the correction for continuity of the chi-square test, a linear-by-linear association test, and Fisher’s exact probability test, based on the application criteria. The significant results of these tests will be complemented with a confidence interval set at 95% for percentage differences.

Regarding the numerical variables between two groups, the Student’s t-test of independent samples for mean comparisons will be carried out, once the requirements of randomness, normality (Kolmogorov-Smirnov’s test, or Shapiro-Wilks’ test, according to the sample size) and equality of variances (Levene’s test) are validated. In case this one is not achieved, the Student’s t-test for independent samples with Welch’s correction will be carried out. In case normality requirements are not accomplished, the Mann-Whitney’s U test will be applied.

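### The 512-woman sample size contains no design effect although health centres are randomised, so a valid cluster-adjusted analysis has less than the stated 80% power for any positive intracluster correlation

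*Protocol article*

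**What the plan says.** Protocol article, *Study sample size*: the control rate is set by "Taking into account that the EB rate in Andalusia is 25%, this is considered the expected value in the control group". The effect is given as "An estimated increase effect of 12% of the EB rates at 6 months is established". The error rates follow: "a two-tail hypothesis is set out, with a power of 80% and assuming a type I error of 5" per cent. The result is "assuming a loss of 10% in the follow-up, the necessary sample increases to 512 women, 256 in each group". The section mentions no ICC, centre size, number of centres or design effect.

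The same article describes the design in *Study design* as follows: "This is a multicentric cluster randomized controlled trial with a control group and an intervention group, without blinding". *Analysis* repeats it: "Individual health centres are the randomization units and the mother-newborn dyad will be the analysis unit". The effectiveness comparison at 6 months, also in *Analysis*, is a Fisher's exact test of the two groups with no term for centre.

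*Randomization and data management* adds that, after the centres are randomised, women are randomised again by a simple scheme. It also gives the purpose of the arrangement: to avoid the bias that would arise if two women at one centre were in different groups.

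**The concern.** When whole centres are allocated, women at the same centre tend to resemble each other. They share a midwife, a local population and, in the intervention arm, the same support group. Each woman then adds less independent information than she would under individual randomisation. A sample size that ignores this overstates the power.

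If the analysis is later adjusted for centre, as it should be, a null result could be read as absence of effect when the trial could reliably detect only a difference larger than 12 points. If the analysis is left unadjusted, a positive result could come from centre-to-centre variation.

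**Working it through.** **Inputs from *Study sample size*:** control rate 0.25; increase 0.12, so 0.37 in the intervention arm; two-sided alpha 0.05; power 0.80; loss 10%. The increase is read as absolute. As a relative increase (25% to 28%) the formula would need 3,397 per arm, which is nowhere near the stated number.

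**Step 1: reproduce 512.** Pooled two-proportion formula, mean rate 0.31:

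n = [1.960 × √(2 × 0.31 × 0.69) + 0.842 × √(0.25 × 0.75 + 0.37 × 0.63)]² / 0.12² = 232 per arm.

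232 × 1.10 = 255.2, rounded up to 256 per arm, or 512 in total. Dividing by 0.90 instead gives 258 per arm, or 516, an immaterial difference. The stated inputs use up the whole figure.

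**Step 2: power without clustering.** 256 less 10% is 230 evaluable per arm.

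Power = Φ{[0.12 − 1.960 × √(2 × 0.31 × 0.69 / 230)] / √[(0.25 × 0.75 + 0.37 × 0.63) / 230]} = 79.7%.

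The exact power of Fisher's test at this size is 77.0%.

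**Step 3: power with clustering, adjusted analysis.** The article gives neither the number of centres K nor the ICC, so both are assumed. Evaluable women per centre: m = 0.9 × 512 / K. Design effect: DE = 1 + (m − 1) × ICC. Power is the Step 2 formula with 230/DE in place of 230. For K = 20, m = 23.04; at ICC 0.02, DE = 1 + 22.04 × 0.02 = 1.44, and 230/1.44 is about 160 effective women per arm.

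| Centres (assumed) | ICC 0.01 | ICC 0.02 | ICC 0.05 |
|---|---|---|---|
| 40 (m = 11.5) | 76% | 72% | 62% |
| 20 (m = 23.0) | 71% | 64% | 48% |

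The difference from 25% that is detectable at 80% power with 20 centres is 14.6 points at ICC 0.02 and 17.8 points at ICC 0.05. These are normal approximations with equal centre sizes; few or unequal centres would make them worse.

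**Step 4: the planned unadjusted test.** Ignoring centre leaves the critical value at 1.960 while the true standard error grows by √DE. Approximate type I error is 2Φ(−1.960/√DE). With 20 centres this is 10% at ICC 0.02 (DE 1.44) and 18% at ICC 0.05 (DE 2.10). Rejection under 25% against 37% is then about 75% and 72%. Fisher's test is somewhat conservative, so its exact values would be a little lower.

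**Step 5: control rate, as a sensitivity check.** The 25% is described as an Andalusian rate, whereas the trial enrols "Healthy women with exclusive or partial breastfeeding 10 days after birth". A higher control rate is therefore plausible. At an illustrative 35.2%, with 230 per arm and no clustering, power is 74.5% if the effect stays at 12 points (47.2%). It is 84.8% if the odds ratio implied by 25% against 37% (1.76) is kept, giving 48.9%.

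**The case against.** The strongest objections concern size and reach.

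- **The shortfall cannot be fixed from the article.** With 40 centres and ICC 0.01 the loss is only about 4 points. A condensed article may also leave the number of centres and women per centre to the full protocol, so their absence is no fault in itself. This stands. It does not rescue the stated figure, because the inputs reproduce 512 exactly with no design effect, and a fuller document could not add one without changing 512 or the power.
- **The power losses in Step 3 presuppose a cluster-adjusted test, which the article does not plan.** This also stands. Under Fisher's exact test as written, the chief consequence is false positives.
- **The second, simple randomisation of women might suggest individual allocation, with no need for a design effect.** The wording is in conflict and needs reconciling. However, the aim stated in that same section keeps women of one centre in one group, and *Analysis* names centres as the randomisation units.
- **A reader might infer that the control rate is itself wrong and independently costs power**, for instance by dividing 25% by 71% to get 35%, or the 28.5% national figure in *Discussion* by 71% to get 40%. The documents do not support that. *Background* places the 71% after hospital discharge and *Discussion* places it at 6 weeks; neither is the 10-day eligibility point. As Step 5 shows, even the direction of the effect on power depends on whether the difference or the odds ratio is held constant.

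**Conclusion.** The point holds for the missing design effect. That 512 is the individually randomised number is a matter of arithmetic and needs no outside assumption. With the plan's own 10% loss there is no slack (79.7% at ICC zero), so a valid cluster-adjusted analysis falls short of 80% for any positive ICC. The direction is firm. The size is conditional: roughly 48% to 76% power across 20 to 40 centres and ICC 0.01 to 0.05, all of these assumed. The mismatch between the control rate and the enrolled population is a reason for a sensitivity display. It does not by itself show a power shortfall, and no particular replacement rate can be prescribed from this article.

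**What to change.** In *Study sample size*:

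1. State the planned number of centres, the expected women per centre and an assumed ICC range, and apply DE = 1 + (m − 1) × ICC.
2. Restate the power, or the minimum detectable difference, that 512 women deliver, and say that it refers to an analysis that accounts for centre. The effectiveness test in *Analysis* has to match that statement.
3. Add a short sensitivity note showing power over a range of control rates above 25%, naming the scale on which the effect is held constant.
4. Reconcile the simple randomisation of women in *Randomization and data management* with centres as the randomisation units.

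The cost is mainly the rewording of one paragraph, plus matching sentences in the other two sections. The stated power becomes less favourable. No additional enrolment is required, although the change discloses the shortfall and does not remove it.

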### Adverse events

Adverse events are currently not foreseen, due to the study and intervention’s nature.

### Analysis

A complete statistical analysis plan will be previously performed, as well as a report thereof and of the results, according to the Consolidated Standards of Reporting Trials (CONSORT) [35, 36]. The analysis will be carried out on the basis of an intention-to-treat principle, without taking into account whether or not adherence to the breastfeeding support group was completed. Individual health centres are the randomization units and the mother-newborn dyad will be the analysis unit. All statistical trials and confidence intervals will be assumed with a type I error established in alpha = 0.05, using the IBM SPSS V22 statistics package [37].

An exploratory data analysis will be conducted in order to identify atypical values, for the total of our studied sample, as well as for the different sub-groups created. A graphic exploratory analysis of the different studied variables will also be conducted, according to their numerical or non-numerical character. Frequency and percentage distribution scales will be elaborated for the descriptive analysis of variables with a qualitative (non-numerical) character. For the quantitative (numerical) ones, centralization and dispersion measures will be calculated. In variables with a normal distribution, the mean and the standard deviation will be calculated and, in those with an asymmetric distribution, the mean and interquartile range (p25-p75) will be calculated. Furthermore, point estimators and confidence intervals will be calculated at 95% for averages and percentages. The relationship between two qualitative variables will be analysed with Pearson’s chi-square test, the correction for continuity of the chi-square test, a linear-by-linear association test, and Fisher’s exact probability test, based on the application criteria. The significant results of these tests will be complemented with a confidence interval set at 95% for percentage differences.

Regarding the numerical variables between two groups, the Student’s t-test of independent samples for mean comparisons will be carried out, once the requirements of randomness, normality (Kolmogorov-Smirnov’s test, or Shapiro-Wilks’ test, according to the sample size) and equality of variances (Levene’s test) are validated. In case this one is not achieved, the Student’s t-test for independent samples with Welch’s correction will be carried out. In case normality requirements are not accomplished, the Mann-Whitney’s U test will be applied.

Should any statistically significant differences be considered, confidence intervals at 95% for mean differences will be determined. For the comparison of numerical variables between more than two groups, and once the independence, normality, and homoscedasticity requirements are validated, the ANOVA (analysis of variance) test will be conducted; in case the requirements are not achieved, the Kruskal-Wallis’ test will be carried out. Should any statistically significant differences between the means of the different studied sub-groups be detected, multiple comparison tests will be conducted in order to identify between which sub-groups were those differences found, considering a corrected level of alpha significance based on the number of comparisons made. On the survival analysis, the Kaplan-Meier’s non-parametric estimator will be used.

The effectiveness analysis will be conducted through the comparison of the number of women who chose to breastfeed exclusively at 6 months in both groups, using Fisher’s exact test and estimating the confidence intervals of the difference. Should factors be unequal in both groups, an explanatory logistic regression model would be carried out, in which the dependent variable would be exclusive breastfeeding, and the independent one would be the intervention group, adjusted for the potential factor findings. The efficacy analysis would be carried out on an intention-to-treat basis.

In order to avoid the effect of the intervention on the duration of breastfeeding in the support group, a survival analysis will be conducted, which will compare the intervention and control groups using the log-rank test. Control of potential confounders will be made through Cox’s different regression models. All *p* values under 0.05 will be considered as statistically significant.

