#### Randomization and data management

Centres are randomized to either an intervention arm or normal care. After this randomization, women are allocated either to the intervention group or to the control group by simple random sampling at the 35th–37th week of pregnancy by the midwives at the primary health centres, who will confirm that these women have the intention to breastfeed and that they have indeed initiated it in the first 10 days postpartum. Once the centre randomization for the recruitment of women for the control and intervention groups is conducted, these will be once again randomized following a simple randomization strategy. The participants’ recruitment will begin in September 2020, and will end in March 2022. This will be carried out by those midwives responsible for each health centre, being advised by one of the project’s experts.

These experts will work independently of the accountable researchers for the recruitment of participants. They will allocate health centres using a random sequence made by the *Oxford Minimization and Randomization (OxMAR)* system [23]. The experts will randomly assign a non-transferrable identifier to the health centres, making a difference between the control group and the experimental group centres. Subsequently, each participant will have an identification code depending on their group. This way, we intend to avoid the bias between two women attending antenatal care at the same centre who may or may not join the breastfeeding support group linked thereto, depending on whether they are allocated to one group or the other.

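### Health centres are randomised, but every named between-arm test treats women as independent, so the 5% error rate and the 95% intervals are not controlled

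*Protocol article*

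**What the plan says.** The Study design section calls this a "multicentric cluster randomized controlled trial with a control group and an intervention group". Under Randomization and data management, "Centres are randomized to either an intervention arm or normal care". The Analysis section then sets out the units: "Individual health centres are the randomization units and the mother-newborn dyad will be the analysis unit".

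The methods that follow in the same section are all in individual-level form:

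- **Exclusive breastfeeding at 6 months (effectiveness analysis):** Fisher's "exact test and estimating the confidence intervals of the difference". If factors are unbalanced, a logistic regression on intervention group and those factors is added.
- **Breastfeeding duration:** a survival analysis to "compare the intervention and control groups using the log-rank test", with Cox models to control confounders.
- **Numerical variables such as the self-efficacy scores:** a Student's t "test of independent samples for mean comparisons will be carried out", with Welch and Mann-Whitney as fallbacks.
- **Other categorical variables:** chi-square and related tests.

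A type I error of 0.05 is set for all tests and intervals. The article mentions no centre term, random effect, robust variance, frailty, centre-level summary, ICC or design effect.

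**The concern.** When whole centres are allocated, the comparison between arms carries the variation between centres as well as that between women. Fisher's test, the independent-samples t-test and the ordinary log-rank test see only the second part. The trial has clear sources of correlation. Women at a centre have the same reference midwife, and in the intervention arm they also attend monthly sessions that she leads (Description of the intervention). The optional social-media groups may add to this, although the article does not say whether they are specific to a centre.

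The primary p-value, the interval for the 6-month difference, the duration comparison and the self-efficacy comparisons would all overstate the evidence. Recruiting more women in the same centres would not cure this. The results are meant to inform a guide for professionals who set up such groups, so a false positive would have consequences.

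**Working it through.** **1. Does the plan assume independence elsewhere?** Inputs from Study sample size: 25% in the control group, 12 points more (37%) in the intervention group, two-sided 5%, power 80%, 10% loss.

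n per arm = (1.96 + 0.8416)² × (0.25×0.75 + 0.37×0.63) / 0.12² = 7.849 × 0.4206 / 0.0144 = 229.3, so 230. Then 230 / 0.9 = 255.6, so 256 per arm and 512 in total.

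This is exactly the stated figure, and it contains no design effect. The sample size and the tests rest on the same assumption of independent women.

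**2. Approximate size of the error.** With m analysed women per centre, the design effect is DE = 1 + (m − 1) × ICC, and the actual two-sided error of an unadjusted test at nominal 5% is 2 × [1 − Φ(1.96/√DE)]. Neither m nor the ICC is in the article, so the values are assumed.

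- m = 10, ICC 0.01: DE = 1.09, error 6.0%.
- m = 10, ICC 0.05: DE = 1.45, 1.96/√1.45 = 1.63, error 10.4%.
- m = 20, ICC 0.05: DE = 1.95, 1.96/√1.95 = 1.40, error 16.0%.
- m = 20, ICC 0.10: DE = 2.90, error 25.0%.

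**3. Simulation of the named test.** Beta-binomial outcomes, 230 analysed women per arm, true rate 25% in both arms, whole centres of equal size allocated to an arm, 20,000 trials per scenario. The Monte Carlo standard error at 5% is √(0.05×0.95/20,000) = 0.15 points.

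False-positive rate of Fisher's exact test at nominal 5%:

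| Centres per arm (women per centre) | ICC 0.01 | 0.02 | 0.05 | 0.10 |
|---|---|---|---|---|
| 5 (46) | 9.0% | 13.1% | 25.9% | 38.7% |
| 10 (23) | 5.9% | 8.6% | 15.8% | 24.7% |
| 23 (10) | 4.8% | 5.8% | 8.6% | 13.4% |

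With no clustering Fisher's test rejects in only 3.8% to 3.9%, because it is conservative. The true inflation is therefore larger than a comparison with 5% suggests.

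Coverage of the unadjusted 95% (Wald) interval for the difference:

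| Centres per arm | ICC 0.01 | 0.02 | 0.05 | 0.10 |
|---|---|---|---|---|
| 10 | 92.5% | 89.6% | 81.8% | 72.5% |
| 23 | 93.7% | 92.7% | 89.5% | 84.2% |

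**4. Numerical outcomes.** An independent-samples t-test on a normal score with 10 centres per arm (4,000 trials per scenario) gave 8.0%, 10.8%, 17.6% and 29.0% false positives for the same four ICCs.

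**5. Does a centre-level analysis repair it?** In the set-up of step 3, a t-test on centre proportions rejected in 4.7% to 5.2% of trials in every scenario.

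**The case against.** **The size is unknown.** The article gives neither the number of centres nor an ICC, and the largest figures need few centres and an ICC of 0.05 or more. With 23 small centres per arm and ICC 0.01, Fisher's conservatism absorbs the inflation (4.8%). This stands as a limit on the size. The error rate is uncontrolled, which does not prove that any given positive result is false. Even in that favourable case the interval under-covers (93.7%).

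**Women may also be randomised.** Randomization and data management says of the women that "these will be once again randomized following a simple randomization strategy". If women were truly randomised within centres, most between-centre variation would cancel. Under that reading, with clustering left only in the intervention-arm groups, Fisher's test rejects in 4.3%, 5.2%, 6.6% and 9.6% of trials for ICC 0.01 to 0.10 with 20 centres in total, and in 3.9% to 6.2% with 40. The larger figures would then not apply. But this reading conflicts with the Analysis section, which names centres as the randomisation units, and with the stated aim of avoiding bias between women at the same centre who fall in different groups. It also does not remove the problem where the ICC is high.

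**A fuller analysis plan is promised.** It could specify the variance for the logistic and Cox models, which the article leaves open. It could not make Fisher's test, the independent-samples t-test or the ordinary log-rank test allow for centres. It would have to replace the effectiveness test that the article fixes.

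**Analysing dyads is not an error in itself.** That is correct. The fault lies in the methods chosen.

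**Conclusion.** The point holds and must be fixed before outcomes are analysed. As written, a cluster-randomised trial is analysed as if women had been individually randomised, and this affects the primary test and its interval. Under whole-centre allocation, equal centre sizes and 230 analysed women per arm, the real error of the nominal 5% test runs from close to nominal (many small centres, ICC 0.01) to about 25% (10 centres per arm, ICC 0.10) or 39% (5 per arm, ICC 0.10). The article gives no basis for assuming the benign end of that range.

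**What to change.** 1. **Primary analysis.** Replace Fisher's test. One option is a logistic mixed model with a random centre intercept and a small-sample correction, reported as a standardised difference in exclusive-breastfeeding percentage with 95% CI. If centres are few, use a t-test on centre percentages with degrees of freedom from the number of centres.
2. **Other outcomes.** Use linear mixed models with a centre effect for the self-efficacy scores. For duration, replace the plain log-rank test by Cox regression with centre frailty or centre-robust variance, noting that robust variance is itself unreliable with few centres.
3. **Missing data.** Include centre in the multiple-imputation model.
4. **Wording.** Change the sentence on units to: *women are the units of observation; all comparisons account for randomisation by centre*. Reconcile the passage on a second randomisation of women with it, because the centre-level t-test suits only whole-centre allocation. Confirm that the named software can fit the chosen models.

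The cost is a change of analysis text, with no new data. The price is wider intervals and less power. With 230 analysed per arm, power for 25% against 37% would be about 76% (10 women per centre, ICC 0.01), 64% (10, ICC 0.05) or 51% (20, ICC 0.05). Keeping 80% would take 256 × DE per arm: 256 × 1.09, 1.45 or 1.95, rounded up to 280, 372 or 500, which is 560, 744 or 1,000 women in total. The sample size should therefore be revisited with a stated number of centres and ICC, but the analysis needs correcting whatever the answer.
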